### Economic evaluation

A health economic analysis plan will be developed, reviewed and approved by the TSC prior to data analysis. A within-trial cost-utility analysis will present the incremental costs per quality-adjusted life year gained of older people with TR-GAD receiving tailored ACT plus UC compared to UC alone from an NHS and social care perspective. Costs will be estimated on a per-participant basis and will include costs for delivering the intervention. The modified CSRI will be used to collect data on health and social care resource use. Unit costs will be derived from relevant national sources and will include NHS reference costs and Personal Social Service Research Unit costs [48]. The standard version of the EQ-5D-5L will be used to collect patient reported health status. Values for EQ-5D-5L for England will be used based on NICE advice at the time of analysis, which may either be to use the value set currently in collection or a mapping approach. These will be calculated using the area under the curve method. Appropriate multiple imputation techniques will be implemented where data on the EQ-5D-5L or resource use are missing. Differences in costs and quality-adjusted life years between the treatment arms will be described and the incremental cost effectiveness ratio, with associated uncertainty, will be calculated.

Clinical effectiveness data will be used to judge whether there is evidence of continued benefit from the treatment at 12 months and any evidence of a waning of effect. This will determine if there are grounds to extrapolate the analysis beyond the 12 months observed period using a simple decision model to estimate costs and benefits. This may be important since continued health benefits are unlikely to be matched by increased costs, given the upfront costs of providing the intervention. The time period for the model or appropriate methods for extrapolation cannot be determined at this stage. Any model based extrapolation will adhere to standard methods to reflect uncertainty including probabilistic sensitivity analysis and one-way/multi-way analyses. A separate analysis of over-the-counter medication will also be conducted in order to assess whether there are significant differences between treatment arms. A sensitivity analysis including these costs will be conducted if differences are non-negligible. Similar analyses will be conducted for capability-adjusted life years from the ICECAP-O.

With respect to the pooling of UK and Australian data, the base case analysis will pool data on both outcomes and resource use from all participating sites in the UK and Australia as usual care and health systems are considered to be similar in both countries and resource use is expected to be comparable. UK-specific unit costs and UK/England EQ-5D index scores will be applied to the participant level data and the analysis will proceed on the full dataset, maximising use of the trial data. Multilevel modelling of costs and outcomes will be used in a sensitivity analysis, to explore the potential impact of clustering at the national and/or therapist level. An exploratory analysis of treatment effect will be conducted by country of recruitment.

### Mixed-methods process analysis

An informal mixed-methods process analysis will be conducted to examine perceived mechanisms of impact, facilitators of and barriers to implementation, and contextual factors. Qualitative data from the qualitative satisfaction questionnaire, completed by older people with TR-GAD at 6-months follow-up and trial therapists at the end of their involvement in the study, will be transcribed verbatim and anonymised to maintain confidentiality. Data will be analysed iteratively using focussed thematic analysis [49, 50]. Two members of the research team will independently code initial questionnaires using the computer programme, NVivo, before constructing an analytical framework around: i) the acceptability, suitability, relevance, perceived benefits and limitations, perceived mechanisms of impact, and facilitators of and barriers to implementation of ACT for older people with TR-GAD for those in the intervention arm; and ii) the psychological support received, what was felt was needed, and the helpfulness of psychological support for those in the usual care arm. The analytical framework will be applied to the remaining questionnaires, with themes and subthemes being refined as necessary. Ideas about themes and relationships will be discussed with PPI representatives. Findings will be used to make further refinements to the intervention, particularly with respect to implementation in clinical practice.

Quantitative data relevant to the process analysis will focus on four key areas: intervention uptake, treatment fidelity, reach and outcomes. Data collected on number of sessions attended, modality of sessions, use of interpreters and reasons for non-attendance will be analysed to explore what contextual factors (such as participant sociodemographic and clinical characteristics at baseline) may influence uptake of the intervention. Data collected on ACT consistency and inconsistency scores from the ACT Fidelity Measure will be analysed to explore what contextual factors (such as therapist characteristics at baseline and mode of delivery) may influence treatment fidelity. Sociodemographic data from the trial will be analysed to explore reach and uptake in eligible populations in diverse settings and identify any under-represented populations through comparison with Office of National Statistics area level census data. Sensitivity analyses and additional exploratory analyses will identify what contextual factors (such as clinical characteristics at baseline) are associated with variations in primary and secondary outcome data.

### Trial oversight

The study will be conducted in line with the Helsinki Declaration. North London NHS Foundation Trust (formerly Camden and Islington NHS Foundation Trust) is the nominated sponsor and will lead research governance. The study will be conducted in accordance with the protocol, SCTRU SOPs and Good Clinical Practice. Three committees will govern the conduct of the trial: the TMG, TSC and DMEC. The TMG will comprise co-applicants, collaborators, PPI representatives, and trial staff. It will initially meet monthly via video call and then every 2–3 months as the trial progresses. The independent TSC will comprise academic clinicians, a statistician, a health economist and PPI representatives, while the independent DMEC will comprise academic clinicians and a statistician. Both groups will meet every 6–12 months to review progress and monitor the trial, with safety data additionally being reviewed by the DMEC.

### Safety

Adverse Events (AEs) and Serious Adverse Events (SAEs) can be reported by trial sites at any stage of trial participation, including by participants at 6- and 12-months follow-up, in accordance with SCTRU SOPs. An AE will be defined as any untoward medical occurrence in a trial participant with TR-GAD. Categories of AEs and SAEs are shown in Table 4. All SAEs will be reported to the SCTRU and the sponsor within 24 h of discovery at the trial site. SAEs will be rated in terms of seriousness, intensity, frequency, relationship to the intervention and expectedness. Those deemed both “unexpected” and “related” to the intervention will be reported to the REC within 15 days of being reported to the trial team. In addition, the Australian research team will report SAEs for participants recruited from Australian sites to their Research Governance Office within 72-h, in line with National Health and Medical Research Council requirements. Compensation to UK and Australian participants who suffer harm from participation in the trial will be available through insurance held by North London NHS Foundation Trust and Macquarie University, respectively.

**Table 4 Tab4:** Definition of adverse events (AEs) and serious adverse events (SAEs) in the trial

Type of event	Categories
AE	Any new co-morbid psychiatric condition reported
	Any reported event that has significantly affected the psychological health status of the participant (e.g. a stressful life event such as a bereavement)
	New reports of suicidal ideation with or without active suicidal behaviour/plans, but without intent during the trial (i.e. not reported at baseline)
	Other
SAE^a^	New reports of suicidal ideation with active suicidal behaviour/plans and intent
	Reports of physical self-harm
	Requires unplanned in-patient hospitalisation^b^
	Requires prolongation of existing hospitalisation^b^
	Is life-threatening^c^
	Results in persistent or significant disability or incapacity
	Results in death
	Considered medically significant by the investigator

^a^All of the SAEs defined here will be classified as unexpected

^b^Hospitalisation is defined as an inpatient admission, regardless of length of stay, even if the hospitalisation is a precautionary measure for continued observation

^c^A ‘life-threatening’ event refers to an event in which the participant was actually at risk of death at the time of the event

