### Intervention

Participants will be offered up to 14 one-to-one sessions of tailored ACT, each lasting up to one hour, over six months plus a booster session at approximately 3-months post-intervention. There will be a phased ending to the sessions, such that they are approximately weekly for the first 12 sessions and then approximately fortnightly thereafter, to facilitate ending of sessions. Partners or family members will be invited to attend all sessions, with the participant’s consent. However, sessions will be focused on the participant rather than other attendees. Sessions will be delivered face-to-face (within the outpatient clinic, GP surgery or participant's home), or via video call or telephone (if video call is not available), depending on participant preference, therapist availability and service restrictions. Sessions will be delivered by Band 6–8 clinical psychologists, counselling psychologists, psychotherapists or high-intensity CBT therapists (or their equivalent in Australia) who are based in primary or secondary care services, with a minimum of one year of experience of delivering psychotherapy interventions.

As shown in Table 2, sessions will focus on the six core processes in ACT. Suggested skills, metaphors and/or experiential exercises, audio files and home practice tasks tailored to the needs and preferences of older people with TR-GAD are specified in each session. However, therapists are given the choice of what order to deliver the sessions in (based on the case conceptualisation), which ACT metaphors and/or experiential exercises to use (and personalise) in each session, and the pace of the sessions (based on individual needs and preferences). The booster session at 3-months post-intervention will review ACT skills and strategies discussed in the sessions and will be conducted after the outcome assessment at 6 months follow-up in order to avoid biasing outcomes at this timepoint.

**Table 2 Tab2:** Outline of the tailored ACT intervention for older people with TR-GAD

**Session**^a^	**Main focus of the session**^b,c^	**ACT metaphors and/or exercises**
1	Assessment of current issues, goals for therapy and introduction to ACT	1) Choice point model
2–13^d^	Clarifying values (i.e., what a person wants to be doing and the way in which they want to be doing that)	1) Lifetime achievement award, Values list or Values questions

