Secondary outcome measures will be completed at the same time points, unless otherwise stated, and will include:McGill Quality of Life Questionnaire-Revised [26]: This is a self-report measure of quality of life that has good psychometric properties. It comprises 14 items forming 4 subscales: Physical (3 items), Psychological (4 items), Existential (4 items) and Social (3 items);Geriatric Depression Scale-15 [27]: A 15-item self-report measure of depression developed specifically for older people;Comprehensive Assessment of ACT processes (CompACT) [28]: A 23-item self-report measure of psychological flexibility, which ACT aims to develop. It has 3 subscales: openness to experience (which explores one’s willingness to experience thoughts, emotions, sensations, etc.), behavioural awareness (which assesses mindful awareness of one’s actions), and valued action (which examines engagement in meaningful activities);Health and social care resource use, including dose and frequency of prescribed and non-prescribed medication: This will be captured using a modified CSRI [24];EQ-5D-5L plus EQ-VAS [29]: A 5-item self-report measure and visual analogue scale measure of health-related quality of life. The former will be used to calculate utility scores for quality-adjusted life years;ICECAP-O [30]: A 5-item self-report capability measure for older people, which captures benefits to broader wellbeing than just health and will be used to calculate capability-adjusted life years;Adverse events (e.g. falls, new reports of suicidal ideation, deaths, hospitalisations, etc.) at 6- and 12-months follow-up;Satisfaction with ACT plus UC or UC alone: This will be assessed using the Client Satisfaction Questionnaire-8 [31] and will be assessed in both arms at 6-months follow-up in order to avoid unblinding of outcome assessors;Goal-Based Outcomes tool [32]: A self-reported, idiographic outcome measure will be used to assess personally meaningful behaviour change. This asks a person to define three personally meaningful behavioural goals and then rate their progress towards this goal on an 11-point Likert scale (from 0 = not met at all to 10 = fully met);Cognitive & Leisure Activity Scale [33]: A 16-item self-report measure that assesses engagement in 16 types of activities, including cognitive, social, creative and spiritual activities;Adherence (i.e., session attendance after each session for those randomly allocated to the ACT arm).

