**Table 3 Tab3:**
[figure not shown]
Schedule of enrolment, interventions and assessments

*ACT* Acceptance and Commitment Therapy, *PR* post-randomisation, *UC* usual care

^a^As the modified CSRI includes a question about psychological therapies received, this will be administered in one of four ways at follow-up to prevent potential unblinding of outcome assessors: i) returned via post to the central study team; ii) via online methods; iii) by telephone by the non-blind outcome assessor arranging the follow-up visit, with the rest of the assessment being completed by the blinded outcome assessor; or iv) at the end of the outcome assessment session at 12 months, after the outcome assessor has completed the unblinding question

^b^After each session

^c^Serious adverse events can be reported at any time

^d^Completed after consent, but prior to randomisation, after participants are given a rationale for ACT

^e^Completed at the end of involvement in the trial

^f^Assessed on an ongoing basis throughout intervention delivery in 10% of randomly selected sessions

All older people with TR-GAD will be invited to complete an anonymous qualitative satisfaction questionnaire at 6-month follow-up via post, email or online via Qualtrics (or verbally via telephone, video call or face-to-face interview if necessary). Any questionnaires completed verbally will be conducted by an independent member of the local or central research team to avoid unblinding of outcome assessors. There will also be separate versions of the questionnaire for the intervention arm and UC arm to avoid unblinding of outcome assessors. Those in the intervention arm will be asked questions in relation to the acceptability of ACT and its suitability and relevance to older people with TR-GAD, perceived benefits and limitations of the intervention, perceived mechanisms of impact, facilitators of and barriers to implementing the intervention in their everyday lives, and recommendations for revising the intervention. Those in the UC arm will be asked questions in relation to the psychological aspects of their usual care. Questions will focus on what kind of formal and informal psychological support they received (if any), what was helpful and what was not, and what they felt would have been helpful.

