### Statistical methods

A statistical analysis plan will be developed, reviewed and approved by the Trial Steering Committee (TSC) prior to data analysis. The primary outcome will be analysed using multi-level modelling, which will include fixed effect covariates (treatment arm and baseline score) and a random effect covariate (therapist) to account for potential clustering. Separate analyses will be conducted at 6-months (primary analysis timepoint) and 12-months follow-up. The difference between treatment arms in mean GAD-7 total score and its 95% confidence interval will be quantified by the model coefficient. Primary analyses will be by intention to treat, but additional sensitivity analyses will assess the impact of session uptake using complier-average causal effect (CACE) analyses to model the average treatment effect among those who were considered “compliant” with ACT. For the purpose of trial data analysis, completion of seven sessions will be regarded as a minimum number allowable for an adequate exposure to treatment in the protocol, with participants that receive fewer than seven sessions being a deviation from this. As the minimum dose can vary across participants, this will be assessed further using a CACE analysis in which treatment outcome will be examined in relation to the number of sessions received. In addition, sensitivity analyses will examine the consistency of outcomes across sites, baseline GAD severity, age at first onset and baseline psychotropic medication use.

Secondary outcomes will be analysed in a similar manner to the primary outcome. Additional exploratory analyses will be undertaken to assess the consistency of treatment effects across a variety of subgroups. These will include treatment preference and expectations, psychiatric comorbidity, limited or no spoken English skills, country of recruitment and mode of therapy delivery. The impact of contamination (e.g. psychological therapy in the control arm) will be assessed in a per-protocol analysis [46].

It is expected that there will be missing outcome data for some participants, either due to study withdrawal, loss to follow up or death. The number of missing values will be summarised by treatment arm, time point and reason. Multiple imputation using Rubin's rules [47] will be implemented for the primary endpoint. Adverse events will be summarised in terms of the number and percentage of participants experiencing each event and the number of events by treatment arm.

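### Adverse events from scheduled assessments and from any-time site reports go into one by-arm summary, and unequal trial contact may raise the ACT counts for events that depend on disclosure

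*Protocol article*

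**What the plan says.** **Collection.** Three places describe when adverse events (AEs) and serious adverse events (SAEs) are gathered.

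- Outcomes lists as a secondary outcome "Adverse events (e.g. falls, new reports of suicidal ideation, deaths, hospitalisations, etc.) at 6- and 12-months follow-up", with no restriction by arm.
- A footnote to Table 3 says "Serious adverse events can be reported at any time". It names serious events only. The footnotes of that table could be read, but not its grid.
- Safety says that both AEs and SAEs "can be reported by trial sites at any stage of trial participation, including by participants at 6- and 12-months follow-up".

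**Analysis.** Statistical methods says "Adverse events will be summarised in terms of the number and percentage of participants experiencing each event and the number of events by treatment arm". It states no test or effect estimate for harms, and no split by how an event came to light.

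**Contact.** Under Intervention, ACT participants are offered "up to 14 one-to-one sessions of tailored ACT, each lasting up to one hour, over six months plus a booster session", delivered by therapists "who are based in primary or secondary care services". The article describes no matching trial contact for usual care (UC).

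**Definitions.** Several rows of Table 4 count an event only if someone reports it: a new comorbid psychiatric condition, a life event affecting psychological health, new suicidal ideation and physical self-harm. Self-harm, and suicidal ideation with plans and intent, are classed as SAEs. The other rows just named are AEs.

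**The concern.** A harms table by arm is fair only if an event of a given kind has about the same chance of being recorded in each arm. The 6- and 12-month assessments meet that condition. Reports by sites at any stage may not, because one arm has up to 14 + 1 = 15 additional one-to-one meetings with a clinician working in the trial. The disclosure-dependent categories in Table 4 are the kind of thing that people mention in therapy.

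If what is said in sessions reaches the AE forms, ACT could show more events at the same true risk. The Data Monitoring and Ethics Committee reviews safety data. It could then find it hard to tell closer observation from a real excess of suicidal ideation or self-harm, and a real excess could equally be put down to closer observation. The limitations discussed in the Conclusion include assessor unblinding but not unequal ascertainment of harms.

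**Working it through.** The plan gives no expected AE frequency, so there is no harms figure of its own to reproduce. The sample size of 296 is powered on the GAD-7 and does not bear on this point. Only the 148 per arm is used below, to turn percentages into participants.

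**Inputs from the article:** 148 per arm and 20% attrition at 6 months (Sample size); up to 15 trial-therapist contacts in the ACT arm (Intervention).

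**Assumed inputs, not in the article:**

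- *p*: true risk of an event, the same in both arms.
- *d*: share of true events picked up at the scheduled assessments, the same in both arms.
- *s*: share of the remaining events that therapy contact brings to light, in the ACT arm only.

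**Formulas.**

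Reported risk under UC = *p·d*

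Reported risk under ACT = *p·[d + (1 − d)·s]*

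Spurious risk ratio = 1 + *s·(1 − d)/d*, from which *p* cancels.

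The model gives UC no ad hoc reports. Any that occur would pull the ratio towards 1.

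**Spurious risk ratio:**

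| *d* | *s* = 0 | *s* = 0.25 | *s* = 0.50 |
|---|---|---|---|
| 0.95 | 1.00 | 1.01 | 1.03 |
| 0.80 | 1.00 | 1.06 | 1.125 |
| 0.60 | 1.00 | 1.17 | 1.33 |

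**A middle case.** With *p* = 0.20 and *d* = 0.80, UC reports 16.0%. ACT reports 17.0% (*s* = 0.25) or 18.0% (*s* = 0.50). With 148 per arm that is about 24 participants against 25 or 27.

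**A high-end case.** With *p* = 0.25, 60% detected at scheduled assessments and 85% once therapy contact is added, UC reports 0.25 × 0.60 = 15.0% and ACT 0.25 × 0.85 = 21.25%. The ratio is 1.42, or about 22 against 31 participants. Moving from 60% to 85% requires therapy contact to catch (0.85 − 0.60)/(1 − 0.60) = 62.5% of the events otherwise missed, which is a strong assumption.

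**Attrition.** The plan's own 20% is 0.20 × 148 = 29.6, about 30 participants per arm without a 6-month assessment. A UC participant who misses the assessments has no scheduled elicitation of events. An ACT participant who attended sessions before leaving may already have had an event reported. Identical scheduled visits therefore do not by themselves equalise detection.

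**If the summary uses only events elicited identically at 6 and 12 months,** *s* = 0 and the spurious ratio in this model is 1.00.

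**The case against.** The strongest reply is that the AE outcome is already defined at the 6- and 12-month assessments in both arms, and that the Table 3 footnote opens the any-time route to SAEs only. On that reading the non-serious events, which include most of the disclosure-dependent categories, are already collected symmetrically. This has weight, but Safety gives the any-time route to AEs as well, so the three places need reconciling. Even on the narrow reading, self-harm and the more severe suicidal ideation category are SAEs and can still enter by either route.

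Other objections stand and limit the point:

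- The plan describes a summary by arm. A reader might infer a formal between-arm comparison, but no test or estimate is stated. Percentages side by side will still be read as a comparison.
- A reader might infer that therapists feed events into the data. The text names trial sites as reporters and nowhere says that sessions elicit AEs, so detection *may* differ; the article does not show that it does.
- A reader might infer that UC participants are seen only at 6 and 12 months. That holds for scheduled trial contact alone. Comparator describes GP care, medication review, case management and, for a minority, psychotherapy. ACT participants are asked to forgo other formal psychological therapy while UC participants are not, so the gap in clinical contact is smaller than 15 against none.
- Merging of the two routes is inferred from the absence of any split. The analysis plan, the data management plan or the trials unit's procedures may already separate them.
- SAEs are rated individually for their relationship to the intervention and an independent committee reviews safety. It would go too far to say that a real harm could not be recognised.

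**Conclusion.** The point holds as a risk of unequal ascertainment, not as a demonstrated bias. As written, the article allows two reporting routes, gives one arm far more trial contact and tabulates events by arm without separating the routes. The likely direction is towards more reported events under ACT, mainly in the disclosure-dependent rows of Table 4. Deaths and hospitalisations depend much less on disclosure.

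The size cannot be obtained from the article. Under the assumed values the spurious risk ratio runs from about 1.0, when scheduled collection is nearly complete or sessions add nothing, to about 1.4 at the high end. A reader might take the 1.4 as an expected value. The documents do not support that, since it needs both weak scheduled detection and a large contribution from therapy contact.

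The any-time route is a normal safety provision and is not the fault. The weakness is a by-arm table that cannot show which events came through it.

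**What to change.** - Add a source field to the AE form: scheduled 6- or 12-month assessment, or any other report.
- At both scheduled assessments, ask the same AE questions in both arms, so that together they cover the whole period since randomisation.
- Present the by-arm summary of those elicited events beside the by-arm summary of all reports, and show the other reports by source.
- Leave SAE reporting unchanged.
- State the unequal trial contact as a limitation of the harms data.
- Reconcile Outcomes, the Table 3 footnote and Safety on whether non-serious AEs are collected only at 6 and 12 months or at any time.

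The cost is one form field and one extra table. The source of a report is hard to reconstruct later, so the field should be added as early as possible. The scheduled-only summary depends on recall and misses events in participants who die or are lost to follow-up, with 20% attrition assumed at 6 months. That is why the all-reports table has to stay beside it.

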### Eligibility criteria

#### Older people with TR-GAD

Inclusion criteria:Aged ≥ 60 years.GAD diagnosis identified using the Mini-International Neuropsychiatric Interview [22].Since there is no universally agreed definition of TR-GAD in older people, it will be defined here as GAD that has failed to respond adequately (i.e., continued symptoms of GAD that are still causing difficulties) to pharmacotherapy and/or psychotherapy treatment, as described in step 3 of the UK’s stepped-care model for GAD [5]. Those who have been offered treatment and did not want to start it or continue it and are still symptomatic will also be included in this definition. An equivalent definition will be used in Australia. If a person has remitted and then relapsed in relation to GAD, any treatment received prior to remission will not be considered when deciding whether they meet criteria for TR-GAD.Living in the community (i.e., domestic residences or assisted living facilities, but not care homes).

Exclusion criteria:Judged to lack capacity to provide fully informed consent to participate in the trial.A diagnosis of dementia or intellectual disability using standard diagnostic guidelines or clinically judged to have moderate or severe cognitive impairment.A diagnosis of an imminently life-limiting illness where they would not be expected to survive the duration of the trial.Expressing suicidal ideation with active suicidal behaviours/plans and active intent, as assessed using the Columbia-Suicide Severity Rating Scale Screener [23].Currently receiving a course of formal psychological therapy delivered by a formally trained psychologist or psychotherapist, or unwilling to refrain from engaging in formal psychological therapy should they be randomly allocated to the ACT arm.Self-report receiving ACT in the FACTOID feasibility study [19].Having already been randomised in the CONTACT-GAD trial or living with another person who has already been randomised in the trial.Taking part in clinical trials of other interventions for GAD.

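### Table 4 has no suicidality category for baseline ideation that worsens but stops short of intent, although the entry criteria admit people with such ideation

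*Protocol article*

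**What the plan says.** Four places in the protocol article bear on this.

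- **Eligibility criteria, exclusions.** The suicidality exclusion is "Expressing suicidal ideation with active suicidal behaviours/plans and active intent, as assessed using the Columbia-Suicide Severity Rating Scale Screener". Ideation that falls short of this combination does not bar entry.
- **Safety, Table 4, AE rows.** The only suicidality row is "New reports of suicidal ideation with or without active suicidal behaviour/plans, but without intent during the trial (i.e. not reported at baseline"). Two other AE rows could receive a related event: "Any reported event that has significantly affected the psychological health status of the participant", which the table illustrates with a bereavement, and a row labelled Other. The text above the table sets a general definition: "An AE will be defined as any untoward medical occurrence in a trial participant with TR-GAD".
- **Safety, Table 4, SAE rows.** The ideation row is "New reports of suicidal ideation with active suicidal behaviour/plans and intent", without the baseline parenthesis. Other SAE rows include "Reports of physical self-harm", unplanned hospitalisation, life-threatening events, death, and "Considered medically significant by the investigator".
- **Outcomes and Statistical methods.** The secondary outcomes list "Adverse events (e.g. falls, new reports of suicidal ideation, deaths, hospitalisations, etc.) at 6- and 12-months follow-up". The analysis is descriptive: for each event, the number and percentage of participants affected and the number of events, by arm.

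**The concern.** The non-serious suicidality event is defined by absence at baseline, while the entry criteria admit people in whom ideation is already present. For them, a change from ideation alone to ideation with plans or behaviour is a clinically meaningful deterioration, yet neither suicidality row describes it.

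Baseline ideation is a realistic case here. The Recruitment section says that many older people with GAD reach services under a diagnosis of depression with anxiety, and it carries forward people whose anxiety and depressive symptoms trouble them equally.

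Two things are at stake. First, new suicidal ideation is a named example within the adverse-event outcome, and the DMEC reviews safety data. If worsened ideation is filed elsewhere, the ideation line by arm may understate how often suicidality worsened. Second, about 15 sites in two countries would each have to choose among a residual row, a row illustrated by life events, and a discretionary serious row. The same event could be coded in different ways.

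**Working it through.** The article gives no figure to reproduce, so the check sets the entry rule beside the event rows.

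**Step 1: who can enrol.** The exclusion needs ideation, active behaviours or plans, and active intent together. Two states that remain eligible are (a) ideation alone and (b) ideation with plans or behaviour but no intent.

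**Step 2: which row receives each course during the trial, on the plain wording.**

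| At baseline | During the trial | AE ideation row | SAE ideation row | Where it can be recorded |
|---|---|---|---|---|
| No ideation | Ideation, with or without plans, no intent | Yes | No (no intent) | AE ideation row |
| Ideation alone | Ideation with plans or behaviour, no intent | No (ideation was reported at baseline) | No (no intent) | Other, psychological-health row, or medically significant SAE |
| Ideation alone | Ideation with plans or behaviour, and intent | No (intent present) | Yes | SAE ideation row |
| Ideation with plans, no intent | Same, plus intent | No (intent present) | Yes | SAE ideation row |
| Any | Self-harm, unplanned hospitalisation, life-threatening event, death | Not needed | Not needed | Its own SAE row |

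Only the second course lacks a suicidality category. In the third and fourth, the SAE row's requirement of a new report causes no difficulty: ideation with plans and intent is an exclusion at entry, so reaching that state later is always new.

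**Step 3: effect on the table of results.** Statistical methods summarises each event by arm. Assuming the event categories follow the rows of Table 4, an event filed under Other or psychological health stays in the safety tables but not in the ideation line.

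**Step 4: scale.** The article gives neither the prevalence of baseline ideation nor a rate of worsening. Taking the prevalence p as an assumption, with N = 296 and 148 per arm, the number for whom the AE ideation row is closed is N × p:

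- p = 10%: 296 × 0.10 = 29.6, about 30 (148 × 0.10 = 14.8, about 15 per arm)
- p = 20%: 296 × 0.20 = 59.2, about 59 (148 × 0.20 = 29.6, about 30 per arm)
- p = 30%: 296 × 0.30 = 88.8, about 89 (148 × 0.30 = 44.4, about 44 per arm)

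These are people to whom one row cannot apply on the strict reading. They are not misfiled events. Misfiled events arise only in those who worsen and stay short of intent, and that number cannot be obtained from the article.

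**The case against.** The strongest reply is that nothing is lost from safety capture. The general AE definition has no baseline restriction, Other is open to any event, and the psychological-health row could take worsened ideation. The investigator can also declare such a change medically significant and so serious. The gravest courses are SAEs whatever the baseline state. **This stands.** It rules out a stronger reading that a reader might infer from the parenthesis: that participants who enter with ideation and then worsen go uncounted, so that harm is hidden in those at highest risk. The article does not support that. Ideation with plans and intent is excluded at entry, and progression to it is an SAE. What the reply does not answer is classification: an event under Other is counted, but not as suicidality.

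A second reply is that the parenthesis may refer to the particular presentation rather than to ideation as such, so that plans first voiced during the trial are a new report even where ideation alone was present before. **This is a possible reading, and it stands in part.** The text does not settle it. Two defensible readings that place the same event in different rows are themselves a reason to clarify.

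A third reply is that the article condenses a longer protocol and defers to the trials unit's procedures, which may say how worsening of a pre-existing condition is coded. **This tempers the point but does not remove it.** The point concerns a restriction that Table 4 states, not a detail it omits. If guidance elsewhere counts worsening as suicidality, it departs from the plain wording of this row and the two should be aligned.

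A fourth reply is that the rule is the same in both arms and the analysis is descriptive. **This stands as regards the comparison:** no bias between arms is shown. It does not restore events missing from the ideation line in either arm.

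**Conclusion.** The point holds in a limited form. On the plain wording of Table 4, worsening of baseline ideation that stops short of intent has no suicidality category. It can be recorded only in a residual row, the psychological-health row or a discretionary serious row. The ideation count by arm may therefore be understated, and coding may vary between sites.

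The size is unknown. The illustration of 30, 59 or 89 participants rests on assumed prevalences of 10%, 20% and 30% and bounds only the group to whom the row is closed. The conclusion also assumes that the parenthesis refers to ideation in general and that the reported categories follow Table 4.

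A reader might go further and infer a distorted comparison of harm between the arms. The article gives no basis for this: the definition does not depend on allocation, and nothing shows that baseline ideation or its worsening would differ by arm. No efficacy conclusion depends on this row. The change is still worth making, because suicidality is a named safety item and the repair is small.

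**What to change.** Extend the parenthesis in the AE ideation row so that it covers ideation absent at baseline **or** more severe than at baseline, for example newly including active behaviour or plans. Judge severity against the category recorded on the baseline screener. In the results, tabulate new-onset and worsened ideation as separate lines by arm, so that the present definition can still be read off.

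The reference point exists, because the screener is used to determine eligibility. The follow-up information is largely implied too: sites must already establish whether plans and intent are present in order to choose between the AE and SAE ideation rows. The schedule table is not reproduced in the text at hand, so whether the screener itself is repeated at follow-up should be checked.

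The cost is one line in Table 4, a small change to the AE form guidance and a slightly higher AE count. If recruitment has begun, ideation events already filed in other rows should be reviewed against the clarified wording. The change concerns how events are recorded and tabulated, not how participants are managed.
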